## Objectives

The primary objective of this study is to evaluate the effect of a MAR protocol compared to treatment as usual on perceived background pain in adult burn patients admitted to the Intensive Care Unit of the University Hospital Fundación Santa Fe de Bogotá.

Secondary objectives are:

To examine the effects of the MAR on the patients' anxiety and depression levels.To examine the effects of the MAR on the patients' vital signs (heart rate, respiratory rate, oxygen saturation, blood pressure).To examine the effects of the MAR on the patients' medication usage (complementary or rescue doses).To examine medical and social factors, which might be associated with the effects of the MAR.To describe the effects of the MAR on neurophysiological parameters in a few patients in the intervention group (exploratory part of the study).

We hypothesize that the MAR protocol plus treatment as usual—as compared to treatment as usual alone—will lead to lower levels of perceived background pain and will positively impact the patients' mental health, vital signs, and medication usage.

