### Data Collection and Outcome Measures

Basic socio-demographic and medical data will be collected from all participants, including age; gender; educational level; marital status; level of support by the patient's social system; medical diagnosis; type and location of the burns; and depth and surface % of the burns.

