### Primary Outcome Measure

Primary outcome measure is a Visual Analog Scale (VAS) of 0-10. 0 indicates a state without any pain and 10 indicates the most severe pain possible. Each number from 0 to 10 is distributed in a line 1 cm apart and the patient can mark the intensity of pain felt at the time of filling out the VAS. The VAS will be applied at baseline, and every time before, after, and at 3 h post-each intervention. Period of data collection: maximum 2 weeks from the point of study entry.

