### Secondary Outcome Measures

The Colombian version of the Hospital Anxiety and Depression Scale (HADS) (45) will be applied to measure anxiety and depression levels of the participants. The HADS consists of a 7-item anxiety subscale and a 7-item depression subscale rated on a four-point Likert scale. The higher the total points on each scale, the greater the risk of a depressive or anxiety disorder, with a maximum score of 21 for each subscale. The HADS scale will be applied at baseline, after the third, and after the last intervention. Period of data collection: maximum 2 weeks from the point of study entry.Vital signs (heart rate, respiratory rate, oxygen saturation, blood pressure) will be measured via hospital monitors before the intervention, after the intervention, and at 3 h post-intervention. Period of data collection: maximum 2 weeks from the point of study entry.The use of pain medication refers to the frequency and dose of additional analgesic medications requested by the patient during the study period (complementary or rescue doses). The total amount of dosage and frequency will be calculated by summing up individual records. Period of data collection: maximum 2 weeks from the point of study entry.

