### Data Management and Statistical Analysis

Data collection and storing will be done manually and later transcribed to an electronic database. The accuracy of data transcription will be checked by randomly selecting 20% of the participants for whom a double-data entry procedure will be implemented as a means for control of potential errors while transcribing the results from the paper questionnaires to the electronic database. The original questionnaires will be stored in a locked shelf inside the ICU and digital data storing and processing follows the institutional guidelines for data security, including a password protected laptop, encrypted files, and using secure methods of file transfers.

Data analysis will be performed by analysts blinded to the randomization outcomes and based on an intention-to-treat analysis (ITT) (49). Basic socio-demographic and medical data will be analyzed using descriptive statistics and compared between the two groups to detect any differences in the population. For the differences of the main outcome measure (pain) and the secondary outcome measures (anxiety and depression, vital signs, use of analgesics), ANOVA (analysis of variance), the *p*-value test, and the Mann-Whitney *U*-test will be performed. When analyzing the data, a univariate analysis will be carried out in which the frequency (absolute and relative), percentages and confidence intervals of the different qualitative variables will be established. Subsequently, the association between the different variables will be evaluated through the Chi-square χ^2^ test. Additionally, the Shapiro Wilk test will be used to determine the distribution of the quantitative variables. Once this result is obtained, we will seek to determine the mean, standard deviation, central tendency, and dispersion for the variables of normal distribution, while the median and interquartile range will be sought for those of non-normal distribution. These variables will be evaluated using the Student's *t*-test or the Mann-Whitney *U*-test according to the distribution. The results will be considered statistically significant when observing a value of *p* < 0.05 (5%). Finally, a multivariate analysis will be carried out where logistic regression will be used to determine the contribution of each of the different quantitative variables in terms of the observed results.

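### The only multivariable analysis is a logistic regression, but every primary and secondary outcome is quantitative and no binary outcome is defined

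*Protocol article*

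**What the plan says.** The last sentence of Data Management and Statistical Analysis (Protocol article) announces a multivariate step in which "logistic regression will be used to determine the contribution of each of the different quantitative variables in terms of the observed results". It names no dependent variable, cut-off, treatment term or interaction.

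The outcomes are set out earlier:

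- Pain (Primary Outcome Measure): "Primary outcome measure is a Visual Analog Scale (VAS) of 0-10".
- HADS anxiety and depression (Secondary Outcome Measures): two scores, "with a maximum score of 21 for each subscale", with no cut-off.
- Physiology (same section): "Vital signs (heart rate, respiratory rate, oxygen saturation, blood pressure) will be measured via hospital monitors".
- Rescue analgesia (same section): "The total amount of dosage and frequency will be calculated by summing up individual records".

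One of the secondary objectives reads: "To examine medical and social factors, which might be associated with the effects of the MAR". The candidate factors under Data Collection and Outcome Measures include "age; gender; educational level; marital status; level of support" from the social system, then diagnosis, then "type and location of the burns; and depth and surface % of the burns".

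**The concern.** Three things do not fit together.

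1. **Model and outcome.** A logistic model describes the probability of a category. None of the listed outcomes is a category, so one would first have to be made by cutting a score. The article does not say which score or where.
2. **Model and predictors.** Quantitative predictors are legitimate in logistic regression. But the sentence names only quantitative variables, while many of the recorded medical and social factors are categorical.
3. **Model and objective.** The contribution of a variable to the results is a prognostic association: it shows which patients end up with more or less pain. In a two-arm trial, a factor linked to the effect of MAR is one across whose levels the MAR-minus-control difference changes. That requires a treatment-by-factor term.

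At stake is the multivariable analysis and, through it, the secondary objective on medical and social factors. The first mismatch carries most weight because the article states it outright. The third is secondary.

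**Working it through.** **The article's own figure.** The only proportions in the article are in the sample-size section. With P1 = 0.80, P2 = 0.60 and P = 0.70, its general formula gives

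n = [1.96·√(2·0.70·0.30) + 0.842·√(0.80·0.20 + 0.60·0.40)]² / 0.20² = (1.270 + 0.533)² / 0.04 ≈ 81.25,

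which matches the stated result. (The formula gives a number per arm, whereas the article uses 81 as the trial total; that is a separate matter.) The 80% and 60% restate a 2-point difference on a 10-point scale as percentages of the scale. They are not proportions of patients who respond, so they do not supply the missing binary outcome.

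**Outcomes against model.** VAS: score 0 to 10. HADS: two scores up to 21. Vital signs: monitor readings. Analgesia: summed dose and frequency. The same analysis section compares these by ANOVA, t-test or Mann-Whitney, so it treats them as quantitative until its final sentence.

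**Predictors against model.** Ten characteristics are listed. Age and burn surface percentage are clearly quantitative. Gender, marital status, diagnosis, burn type and burn location are plainly categorical. Education, social support and burn depth depend on coding.

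**Cost of dichotomising.** The article gives neither a cut-point nor an SD, so what follows is illustration.

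- Median split of a normal outcome: relative efficiency 2/π = 0.637. For 81 participants, 81 × 0.637 ≈ 52 effective participants, in this model only.
- Treatment difference of 2 VAS points, 81 participants split equally (40.5 per arm), one value per patient, VAS cut midway between the arm means, so the two proportions are Φ(1/SD) and 1 − Φ(1/SD):

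| Assumed SD | Proportions | Power, VAS as measured | Power, VAS cut in two |
|---|---|---|---|
| 2.5 | 0.655 v 0.345 | 95% | 81% |
| 3.0 | 0.631 v 0.369 | 85% | 66% |
| 3.5 | 0.612 v 0.388 | 73% | 53% |

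The loss is 14 to 20 percentage points.

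**What an interaction could show.** Linear model, 81 participants, 1:1 allocation, binary factor split 50:50, one value per patient. The standard error of the interaction is SD·√(16/81) = 0.444·SD, twice that of the treatment effect, SD·√(4/81). Power for a 2-point interaction is Φ(2/SE − 1.96); the smallest effect detectable with 80% power is (1.96 + 0.8416)·SE.

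| Assumed SD | SE of interaction | Power for 2 points | Detectable interaction | Detectable main effect |
|---|---|---|---|---|
| 2.0 | 0.889 | 61% | 2.49 | 1.25 |
| 2.5 | 1.111 | 44% | 3.11 | 1.56 |
| 3.0 | 1.333 | 32% | 3.74 | 1.87 |

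**The case against.** The strongest reply is that little depends on this sentence. Pain, HADS, vital signs and analgesic use are compared between arms by methods suited to quantitative data, and the regression is a closing multivariable step. That stands: the main comparison is not at fault.

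Second, this is a condensed article, and a dependent variable or cut-point may be fixed in a full protocol or analysis plan that is not shown. That stands in part. A reader might infer that the cut-point would be chosen after seeing the data. The article does not establish this; it shows only that none is stated here, and the analysts are to be blinded to allocation. But the article does fix the type of model, and that type does not match the outcomes it defines.

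Third, the 2-point difference called clinically significant in the sample-size section might serve as a threshold. It is not declared as a responder rule for any patient.

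Fourth, the regression is nowhere tied to the objective on medical and social factors, interaction terms are detail that an analysis plan may hold, and categorical factors do appear in Chi-square tests. This is why the interaction point is secondary. It does not disappear, because no analysis in the section addresses differences in the MAR effect: the Chi-square tests concern associations between variables, and Potential Limitations calls for moderator analyses in the field without planning one here.

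**Conclusion.** The point holds for the multivariable analysis only. The model type that the article fixes does not fit any outcome it defines, and it can run only after an unstated dichotomy. If that were a median split of a normal outcome, about 36% of the information would be lost in this model. All power figures above rest on assumed SDs and one value per patient.

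Two stronger readings are tempting but unsupported. One is that the model would be badly overfitted: about 40 events from a median split over ten characteristics is about 4 events per coefficient. But the sentence admits only quantitative variables, and with just age and burn surface percentage that becomes about 20. The article also does not say that all factors enter together. The other is that prognostic factors would be reported as modifying the MAR effect. That is a risk, not something the article says will happen.

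The article should be changed on this point. A stated secondary objective has no analysis that answers it, while the primary comparison is untouched.

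**What to change.** Replace the logistic regression with a linear model, or a mixed model if repeated values are used, for VAS and HADS. Include treatment and the baseline value, and allow categorical factors.

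For the objective on medical and social factors, fit one interaction at a time:

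outcome = β0 + β1·treatment + β2·baseline + β3·factor + β4·treatment × factor

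Report β4 with its 95% CI and label it exploratory. Where the factor is the baseline value itself, the β2 and β3 terms coincide. Prespecify a short list of factors from data already to be collected, for example burn surface percentage, baseline VAS, baseline HADS and social support. Keep logistic regression only if a responder outcome is defined in advance, with the scale, time point and threshold stated.

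No new data are needed. The article contains no linear or mixed regression model at present, so this adds a model specification and is slightly more than a change of wording. The price is a short factor list and low power for interactions, so an interval that includes zero must not be read as showing that a factor is irrelevant.

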### Ethics and Dissemination

The study was approved by the hospital's ethics committee (CCEI-11234-2019/CCEI-11971-2020) and is registered in Clinicaltrials.gov (NCT04571255). All participants will sign an informed consent to participate in the study, including two additional witnesses. Dissemination of the study results will be realized locally, nationally and internationally through publications, posters sessions and oral presentations at conferences.

## Discussion

This feasibility study investigates the effects of a live MAR protocol provided by a certified music therapist on background pain, anxiety and depression, vital signs, and medication intake in adult burn patients. Other outcome measures correspond to the exploratory feature of this study including EEG, EMG and ECG measurements in 20% of the participants in the intervention group. Pain and impaired mental health are frequent symptoms in burn patients and can negatively affect clinical trajectory and recovery during hospitalization in the ICU and beyond. Music therapy is a non-invasive and cost-effective therapy that has been shown to reduce pain and anxiety levels in several clinical populations, including burn patients (30, 31). MAR techniques are widely used by both music therapists and other health care professionals and have been proven to be effective for a variety of conditions, such as sleep difficulties in adults and elders (50), reducing arousal due to stress (51) or treating depression (52). In pediatric burn patients, a MAR protocol was successfully implemented in a previous RCT (53). As mentioned in the introduction section, MAR and other receptive music listening techniques are much more common compared to interactive music making in this population, which was applied in only two previous RCTs (34, 36). This is because burns of the hand occur more often than burns in other areas of the body (54), which limits the holding and manipulating of musical instruments. But also in case hands and arms are not directly affected by the wounds, movements and engaging in physical activity often causes pain for burn patients. Thus, music listening protocols are clearly indicated in this population and have been chosen also for this study.

The current MAR protocol extends previously used interventions by explicitly using live music based on the principles of entrainment. Entrainment—the conscious synchronization and modification of musical elements in relation to biological rhythms of the patient—can further help to individualize the music and has been shown to improve well-being and reduce symptoms in palliative care (55), pediatric surgery (56) or patients with chronic pain (57) for example. A recent study on dynamic rhythmic entrainment found an increase in peripheral blood flow and greater subjective well-being in healthy individuals for entrained music vs. fixed-beat music (58). To our knowledge, this is the first RCT in adult burn patients using a live MAR protocol specifically focusing on entrainment. From other studies it is known that neuronal network oscillations can be entrained by external auditory stimuli and may enhance cognitive and motor function or sleep quality for example (59). Thus, one of the aims of the exploratory part of this study including EEG, EMG, and ECG measurements, is to further explain and/or uncover the basic mechanisms of live and entrained music as a potential stimulus that may help adult burn patients regulate their pain perception. In fact, pain perception has been correlated with changes in brain activation at different cortical regions and is associated with specific physiological frequency bands. For instance, several studies have noted that long lasting pain or tonic pain can induce a reduction in the Alpha frequency band, which can be correlated with the intensity of pain (60). Nevertheless, as the Alpha activity can also be decreased by several other mental tasks, its specificity to pain related processing is still unclear. In the few studies that have addressed correlations between chronic pain and associated brain oscillations, an abnormal decrease of Theta rhythms together with an increase in Alpha and Beta activities in central and frontal regions of the brain have been reported (61). These changes might reflect an alteration of the thalamocortical loops related to the generation of these rhythms, which also play an important role in the integration of sensory information (62). Similarly, they can manifest a modification in the flow of information among cortical networks implicated in pain processing (63). In the case of music, several studies have reported that exposure to music stimuli can entrain brain oscillations in different ranges (64). Moreover, some studies have shown that pleasant music can have a positive effect in external attentional networks and a reduction in internal mind-wandering processes (65). Consequently, we hypothesize that the MAR intervention applied in this study could modulate the expression of particular frequency rhythms having an important role in reducing the network activity implicated in pain perception.

While it is known that music itself can release neurotransmitters and hormones related to pain and stress relief (66), the trauma that many burn patients experience and the inherent link between pain and mental health requires the presence of credentialed professionals, such as music therapists. Profound relaxation can help in self-regulation but may sometimes evoke undesired emotions or thoughts. Stressing the importance of the therapeutic relationship applies also for this study, and time for verbal processing after the MAR will be used to elaborate the experiences during the intervention. While the length of the ICU stay for burn patients can fluctuate, we tried to offer a process-oriented protocol with a maximum of six interventions over the course of 2 weeks. This may not seem a lot, but to our knowledge, all other RCTs on music or music therapy interventions used single interventions or interventions over a few consecutive days) (30, 31).

Another new feature of this study is the focus on background pain instead of procedural pain. While background pain is usually lower in intensity, it is of longer duration and may thus alter pain memory in the long-term (6). This is important, since pain chronification may increase the already higher risks of burn patients in developing mental health impairments, such as acute stress disorder (ASD), post-traumatic stress disorder (PTSD), elevated stress levels, depression, and insomnia (6, 67). Especially in times of an ongoing opioid crisis, complementary treatments to pharmacological strategies for pain management in burn patients are needed not only for procedural pain, but also for background pain (68). In a previous meta-analysis of music interventions and pain in different medical settings, Lee (28) found a statistically significant reduction in opioid intake. However, in the three RCTs found with adult burn however, this result has not been replicated (33, 69, 70). In this study protocol we will try to evaluate total opioid intake during the intervention period, specifically in relation to rescue doses requested by the patients.

## Potential Limitations

We have also identified several potential limitations of this study protocol. First, background pain is influenced by many different factors, such as the medical condition of the patient, the number of procedures, mental health, and social support, among others. This means that a diversity of factors can potentially affect the pain perception of patients. This might be different during procedural pain, in which a more direct relationship between the procedure and the pain experience exists and thus immediate effects of music interventions might be observed more consistently. However, as mentioned at the end of the previous section, background pain in burn patients is an under-investigated topic and may be highly relevant for long-term well-being and health. While an accumulative effect of the MAR intervention over time may lead to an improved relaxation response and coping mechanisms and thus to reduced pain levels and improved mental health, little is known about the ideal dosage or frequency of music interventions. Formal moderator/mediator analyses in the fields of music therapy and music medicine may help in addressing such issues and are clearly needed (71–73).

Another limitation might be the broad inclusion criteria, which could affect the statistical power of the study. This was chosen since recruitment during COVID pandemic might be slower than expected, as ICU beds usually are prioritized for COVID patients during each infection peak. Thus, to keep recruitment within a feasible time frame, this study does not focus on a specific patient group within the burn population.

And third, other outcome measures including EEG, EMG, and ECG measurements are an exploratory feature of this study and due to the small sample size, the results can thus not be generalized. However, we consider them as important first steps in materializing the need for describing potential neurophysiological pathways and mechanisms of live MAR interventions based on the principles of entrainment.

## Conclusion

This is the first RCT on music therapy and pain management for adult burn patients in Colombia—and to our knowledge—also in South America. It is hoped that the results of this study will help gain new knowledge about complementary therapies for burn patients in ICU settings and provide new insights into the effectiveness and the underlying mechanisms of music in health care contexts.

